##### Patient’s Experience of MISSION ABC

Semistructured questionnaires exploring patient experiences, completed after each clinical encounterQualitative interviews will be completed with 10% of patients who participate in the study, exploring factual, structural, interpersonal, intrapersonal, and contextual influences on the experience of receiving the new service. Discussions will be transcribed using a transcription service and analyzed using a thematic analysis to compare themes. A second researcher will review the analysis to ensure all themes are captured.

#### Assessment of Innovations

##### Devices

Acceptability of use of the new diagnostic devices (Niox, FeNO, and Thorasys) as well as the management tools (Flo-Tone and Airsonett) will be analyzed through structured questionnaires given to the clinic staff.Instances where a diagnosis is made as a result of the use of these devices, which would not be identified by standard investigation, will be recorded. If these events are unclear, the decision of the senior clinician present will be considered.Equipment breakdowns or technical difficulties will be recorded as a clinic process outcome.Proportion of patients who have continued to use supportive devices at the follow-up review will be calculated.

##### Digital Platforms

HCPs’ and patients’ experiences of the use of digital platforms will be assessed using semistructured questionnaires.

#### Assessment of Monitored, Supported Follow-Up

Number of patients offered remote monitoring, and proportion of patients who acceptProportion of patients with access to smartphones or home internetNumber of triggers generated on remote monitoringProportion of triggers that result in a clinically significant exacerbationProportion of triggers that require a patient reviewProportion of clinically significant exacerbations that are managed in the communityProportion of responses to remote monitoring that are completed by the patientRate of drop outs from remote monitoring and the stated reasonPatient and primary care experiences of using remote monitoring measured by a semistructured questionnaire

#### Assessment of Health Care Professionals’ Experiences

In addition to the assessments listed above, a sample of 10 HCPs will be invited to participate in a focus group that will explore their views on the acceptability, appropriateness, and feasibility of the program. An independent interviewer will ask them to comment on their perceived barriers and drivers for further implementation of the program. The focus group will be recorded, but the responses will be anonymized. After transcription, the interviews will be analyzed for themes.

#### Participatory Action Research Outcomes

The core team will meet monthly to evaluate the clinic delivery process. Using patient and HCP feedback questionnaires, pitfalls and issues of the clinical process will be examined using Plan-Do-Study-Act analysis. When changes are made, a further review will take place in the following meeting until the change is deemed to have provided a positive impact on the process. These analyses will be recorded in a learning log.

#### Additional Process Outcomes

Rate of uptake of the clinic by primary care providers when offeredExpenditure in delivery of the clinic services including staffing costs, consumables, and unexpected expenses

#### Balancing Measures

We acknowledge that enhanced investigation and intervention may increase costs to health care providers in the short-to-medium term. The following balancing measures will be included as a project outcome:

Number of GP or practice nurse sessions changed or cancelled to host the clinicAdditional costs such as childcare or extra travel incurred by the delivery team when care is delivered remote to their usual place of work or outside the usual working weekNumber of additional GP, community nurse, or emergency department episodes resulting from remote monitoringNumber of additional secondary care referrals resulting from the program

#### Discontinuation or Withdrawal of Participants from Study Treatment

Participants may withdraw at any point in the study.

#### Definition of End of Study

The end of study is the 6-month follow-up after the questionnaires are received from the last participant.

### Data Analysis

#### Description of Analysis Populations

All patients recruited in the study will be included in the analysis population.

#### Analysis of Quantitative Outcome Data

The objective of all analyses is to examine differences in measured variables between time points.

The following comparisons will be made:

Asthma Control Questionnaire, CAT, and AQLQ: baseline as compared to 3 and 6 monthsEmergency care outcomes: 3 and 6 months prior to study as compared to the 3- and 6-month study periodActivation or medicine compliance (ASK-12 and Patient Activation Measure): baseline as compared to 3 and 6 monthsEuroQoL-5D and weight-bearing physical activity: baseline as compared to 3 and 6 months

All the abovementioned variables are continuous measures. Comparisons between time points will be made using the paired *t* test or the Wilcoxon matched-pairs test, depending on the distribution of the changes in outcome between time points.

Summaries of the measures of monitoring and supported follow-up will be prepared (measures outlined above). Patient satisfaction measures will be summarized descriptively. Numbers and percentages will be used for categorical variables, whereas mean and SD or median and interquartile range will be used for continuous variables. Uncertainty in percentages, means, and medians will be quantified by calculating the appropriate 95% CIs.

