### Aims and Objectives

This study aimed to examine (1) the implementation of a novel integrated care model for patients with airways disease and undifferentiated breathlessness using both quantitative and qualitative evaluation of processes and patient and HCP experiences and (2) clinical outcomes throughout the clinic cycles driving a continuous improvement process, evaluated through participatory action research. We also aimed to establish whether MISSION ABC, including innovative diagnostic and self-management tools, can deliver improvements in health service use and clinical outcomes for different patient groups (asthma, breathlessness, and COPD) by comparing the 12-month period prior to the first patient attendance and the 6-month period following attendance, by using regressional analyses to control for seasonal variation bias.

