#### Overall Description of Study Participants

Adult patients (aged ≥ 16 years) with poorly controlled asthma or COPD as well as those with undifferentiated breathlessness will be identified using GRASP tools; referred from a community pharmacist or by their primary care team; and invited to a local MISSION clinic with a relative, friend, or carer in attendance, if they wish. All eligible attendees will be invited to participate in the study. The sample size will be determined by the uptake of appointments and clinic capacity but is projected to be 500 patients and 15 HCPs.

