#### Randomization

There will be no randomization.

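### The aims promise regression to control seasonal bias over a 12-month look-back, but the analysis section fixes 3- and 6-month before/after windows with paired tests that cannot remove a calendar effect

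*Protocol article*

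**What the plan says.** - **Aims and Objectives (Introduction).** Health service use and clinical outcomes are to be assessed by "comparing the 12-month period prior to the first patient attendance and the 6-month period following attendance", and this is to be done "by using regressional analyses to control for seasonal variation bias".
- **Analysis of Quantitative Outcome Data (Data Analysis).** This section opens with "The objective of all analyses is to examine differences in measured variables between time points". Emergency care is compared as "3 and 6 months prior to study as compared to the 3- and 6-month study" period. The method is the paired t test or the "Wilcoxon matched-pairs test, depending on the distribution of the changes in outcome between time points". It mentions no regression, covariate, calendar term or 12-month window.
- **Patient and Health Service Use Outcomes (Longitudinal Follow-Up).** Exacerbations are counted over the 6 months either side of attendance.
- **Disease Control, Disease-Related Quality of Life, and Activation Measures.** Unscheduled care, steroid or antibiotic courses and admissions are recorded at 3 and 6 months, against look-backs of 6 and 12 months.
- **Randomization.** "There will be no randomization". No concurrent comparison group is described for service use.
- **Results.** Funding was in 2017 and enrollment was completed in 2018. The months in which clinics ran are not given.

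**The concern.** The aims name seasonality as a bias and name a remedy. The section that fixes the comparisons contains neither the remedy nor the 12-month window.

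A paired test removes stable differences between patients. It does not remove anything that changes with the calendar for all of them. Two adjacent 6-month windows cover opposite halves of the year for every patient, so the seasonal contrast goes straight into the paired difference. With no control group, nothing else absorbs it. An apparent fall in emergency care could then be partly or wholly the passing of the high season. With the opposite clinic timing, a real benefit could be hidden.

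**Working it through.** **1. The sections side by side**

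| Section | Before | After | Method |
|---|---|---|---|
| Aims and Objectives | 12 months | 6 months | Regression for season |
| Analysis of Quantitative Outcome Data (emergency care) | 3 and 6 months | 3 and 6 months | Paired t or Wilcoxon |
| Patient and Health Service Use Outcomes (exacerbations) | 6 months | 6 months | None named |
| Disease Control… Measures (data recorded) | 6 and 12 months | 3 and 6 months | None named |

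No single analysis satisfies the first two rows. The 3-month look-back needed by the second row is also not among those listed in the fourth.

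**2. Possible size of the bias**

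The article gives no event rate, seasonal amplitude or clinic calendar, so there is no planned figure to reproduce. All inputs here are assumptions: monthly rate 1 + A·cos(2πt/12), with t in months from the seasonal peak, A = 0.2 or 0.3, and no service effect. For a clinic at month c, integrating over each window gives

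- 6 months after: 6 − (12A/π)·sin(2πc/12)
- 6 months before: 6 + (12A/π)·sin(2πc/12)

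with 12A/π = 0.764 for A = 0.2 and 1.146 for A = 0.3.

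| Clinic dates | After/before, A = 0.2 | After/before, A = 0.3 |
|---|---|---|
| End of high season (c = 3) | 5.236/6.764 = 0.77 | 4.854/7.146 = 0.68 |
| Peak or trough (c = 0 or 6) | 6/6 = 1.00 | 6/6 = 1.00 |
| Start of high season (c = 9) | 6.764/5.236 = 1.29 | 7.146/4.854 = 1.47 |
| Even spread over 6 months centred on c = 3 | 5.514/6.486 = 0.85 | 5.270/6.730 = 0.78 |
| Even spread over 12 months | 1.00 | 1.00 |

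In the fourth row the sine term is multiplied by its average over those six months, 2/π = 0.637. The 3-month windows behave almost identically, with a lowest ratio of 0.77 or 0.67.

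**3. Does the 12-month window in the aims cure this by itself?**

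No. Twelve months before averages to a rate of 1. The rate ratio at c = 3 is therefore 5.236/6 = 0.87 or 4.854/6 = 0.81, and at c = 9 it is 1.13 or 1.19. The bias is about halved but not removed.

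**4. Does a season-matched window cure it?**

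Months 12 to 7 before the clinic are the same calendar months as months 1 to 6 after it. Under a stable yearly cycle the two integrals are equal, and the ratio is 1.00 for every A and c. The count for months 12-7 is the 12-month look-back minus the 6-month look-back, both of which are recorded.

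**The case against.** The article condenses a longer document. The analysis section is plainly not a complete list: it omits SF-36, St George's Respiratory Questionnaire, WPAI and other collected measures, and exacerbations too. The regression may be specified in an analysis plan that is not shown, and nothing in the article rules it out. That stands as a reason not to infer that no seasonal analysis will be done. It does not remove the contradiction, because for emergency care the section is not silent: it states windows and tests, and both differ from the aims.

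Four stronger readings are tempting, and the documents do not support them.

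- A reader might infer that any uneven spread of clinic dates produces bias and that only an even 12-month spread avoids it. Under the same model, clinics held at the seasonal peak or trough, or spread symmetrically around either, also give 1.00.
- A reader might infer that a false positive is nearly certain. Simulation with A = 0.2, 500 patients (a sample that "is projected to be 500 patients and 15 HCPs"), an assumed mean of 1 event per 6 months and gamma-distributed patient rates gives 98% rejection by the paired t test, but only with every clinic on the worst date. It is 70% with clinics spread over six months centred on that date, and about 5% with an even 12-month spread. Clinics in at least 10 surgeries with monthly review make a single date implausible.
- A reader might take service use as the main test of the service. No primary outcome is named, and the Study Design summary puts quality improvement and participatory action research first.
- A reader might take the windows as always adjacent and always in opposite seasons. Opposite half-years apply to the 6-month windows only. The abstract also starts follow-up after the last visit, so two-stop patients may have a gap.

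**Conclusion.** The point holds as an internal contradiction with a possible bias of unknown size and sign. The aims promise regression for season over 12 months before and 6 after. The analysis section fixes 3- and 6-month windows and paired tests that cannot deliver it.

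On an assumed sinusoidal rate of 20% to 30% amplitude with no true effect, the 6-month ratio can lie anywhere from 0.77 (20%) or 0.68 (30%), through 1.00, to 1.29 or 1.47, according to when clinics were held. The contradiction needs no assumption. The figures rest on the assumed amplitude, the sinusoidal shape, a stable yearly cycle and a clinic calendar that the article does not give. It should be resolved before the emergency care and exacerbation comparisons are reported.

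**What to change.** Reconcile Aims and Objectives, Patient and Health Service Use Outcomes, the look-backs under Disease Control, Disease-Related Quality of Life, and Activation Measures, and Analysis of Quantitative Outcome Data, so that they state one set of windows and one method. For emergency care and exacerbations, choose one of the following:

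1. **Season-matched comparison.** Months 1-6 after attendance against months 12-7 before, obtained by subtracting the 6-month from the 12-month look-back. A paired analysis can then be kept. The 3-month counterpart (months 12-10 before) cannot be derived from those two totals and would need event dates.
2. **The promised regression.** Specify it with a calendar or season term alongside the before/after term. Use a monthly count model (Poisson or negative binomial, with a patient effect) only if event dates are available. The article does not say that monthly counts or dates are collected.
3. **If neither is done,** withdraw the claim of seasonal control and report the distribution of clinic dates over the year, so that readers can judge the likely direction of bias.

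The cost is modest. Option 1 needs no new data but uses an older comparison period, so it is more exposed to other changes over time. Calendar terms widen the intervals somewhat. Enrollment is complete and analysis under way, so the change must be dated and documented.

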### A New Model of Care

A high proportion of the costs for respiratory diseases is generated by a relatively small group of patients with severe disease (recognized or unrecognized) or complex problems that include multimorbidity, at-risk behaviors, and socioeconomic disadvantage. Such patients often struggle to engage with the structured, proactive care approach to chronic disease management advocated for asthma and COPD, resulting in repeated emergency health care use of both primary and secondary care. An integrated approach for the management of complex patients, incorporating both specialist and primary care teams’ expertise, may be effective in improving outcomes for such high-risk patients. However, the evidence is mixed, and there is a need for evaluations of models of integrated care in routine “real-world” clinical settings.

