#### Patient and Health Service Use Outcomes (Longitudinal Follow-Up)

Changes in quality-of-life measures prior to the clinic visits and at 3 and 6 months were measured with generic or disease-specific quality-of-life questionnaires. These questionnaires evaluated the following:

Changes in productivity and activation measures prior to the clinic visit and at 6 monthsChanges in disease control, quality of life, and comorbidity measured by disease-specific questionnaires and unscheduled health care utilization (eg, emergency GP visits, out-of-hours/111 calls, hospital admissions, and emergency department attendances).Exacerbations in the 6 months before and after MISSION attendanceCost of delivery of the clinic model

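### Emergency-care event counts are declared continuous, and the stated test rule will probably send them to the Wilcoxon test, which does not target total use

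*Protocol article*

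**What the plan says.** In the protocol article, Analysis of Quantitative Outcome Data lists four groups of comparisons. One is emergency-care outcomes, compared over 3 and 6 months before against 3 and 6 months in the study. The section then says of all four groups: "All the abovementioned variables are continuous measures". The test follows from that: "Comparisons between time points will be made using the paired *t* test or the Wilcoxon matched-pairs test, depending on the distribution of the changes".

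Patient and Health Service Use Outcomes (Longitudinal Follow-Up) shows what is being measured: "unscheduled health care utilization (eg, emergency GP visits, out-of-hours/111 calls, hospital admissions, and emergency department attendances". Each is a number of events per patient in a fixed period.

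Two other places bear on the analysis. Aims and Objectives describes "comparing the 12-month period prior to the first patient attendance and the 6-month period following attendance", to be done "by using regressional analyses to control for seasonal variation bias". The list of questionnaires and service-use measures under Patient Assessments sets 3 and 6 months after the clinic against 6 and 12 months before it. The analysis section repeats neither the longer pre-clinic windows nor the regression.

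**The concern.** A count of admissions or 111 calls over 3 or 6 months takes the values 0, 1, 2 and so on, usually with many zeros and a few large values. Calling it continuous is wrong, and here the label matters because it leads to the test.

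The study asks whether the service reduces health service use. The introduction gives the reason: "A high proportion of the costs for respiratory diseases is generated by a relatively small group of patients". For a service decision the relevant quantity is therefore total or mean use, to which heavy users contribute most. A signed-rank test on the changes answers a different question. It discards patients with no change and asks whether the ranks of the remaining changes are balanced around zero. A large fall in a few patients counts only through their ranks, not through the number of events saved. The test also yields no rate ratio. The risk is that a real fall in total use, concentrated where the protocol expects the cost to lie, is reported as no change.

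**Working it through.** **Inputs.** From the protocol: counts as the outcome, paired t or Wilcoxon as the test, equal windows in the analysis section, and a sample that "is projected to be 500 patients and 15 HCPs". The protocol gives no event rate, dispersion, effect size or significance level. The following are therefore assumptions: gamma-Poisson counts with shape 0.7, means of 0.25 to 2 events per window, two-sided 0.05, n=500. There is no figure in the plan to reproduce.

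**1. Which test the rule selects.** The protocol names no normality test or threshold. In simulated paired counts (means 0.2 to 2, dispersion 0.3 to 0.7), a Shapiro-Wilk test rejected normality of the changes in 100% of runs. Any normality-based choice would lead to Wilcoxon.

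**2. How many patients Wilcoxon drops.** With no true effect, the share with zero change is 73% at mean 0.25, 61% at mean 0.5 and 49% at mean 1.0. Many of these patients have no event in either window. That share is (1 + 2m/k)^(-k) for mean m and shape k:
- m=0.25: (1 + 0.5/0.7)^(-0.7) = 0.69
- m=1.0: (1 + 2/0.7)^(-0.7) = 0.39

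**3. The two tests target different quantities.** This is a constructed example, not a forecast. Of 500 patients, 360 are unchanged, 90 rise by 1, 30 fall by 1 and 20 fall by 6.
- Total change: 90 − 30 − 120 = −60 events, or −0.12 per patient.
- Paired t: sum of squares 90 + 30 + 20×36 = 840; variance (840 − 500×0.12²)/499 = 1.669; SE = √(1.669/500) = 0.0578; t = −0.12/0.0578 = −2.08, p=0.038.
- Wilcoxon: 360/500 = 72% dropped. The 120 changes of size 1 have mean rank 60.5 and the 20 of size 6 have mean rank 130.5. Ranks upward: 90×60.5 = 5,445. Ranks downward: 30×60.5 + 20×130.5 = 4,425. p=0.25. The ranks lean towards a rise although total use falls.

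**4. Power when only heavy users improve.** The top 10% of users fall by 40% and everyone else is unchanged.

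| Mean events per window | Wilcoxon | Paired t | Robust rate ratio |
|---|---|---|---|
| 0.25 | 24% | 25% | 27% |
| 0.5 | 32% | 37% | 39% |
| 1 | 52% | 68% | 69% |
| 2 | 74% | 92% | 93% |

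Repeat runs differ by up to about 4 points.

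**5. Power under a uniform fall.** With a 25% fall in every patient at mean 0.5 (dispersion 0.5), Wilcoxon detects it in 83% of trials, paired t in 84% and the rate ratio in 85%.

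**6. Type I error.** Both planned tests reject in about 3% to 6% of runs with no effect.

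**7. Observed time.** With equal windows, if 5% to 20% of patients have only half the post-clinic window observed and are kept, the apparent ratio with no true change is 1 − 0.05×0.5 = 0.975 to 1 − 0.20×0.5 = 0.90. If raw counts over 12 months before are set against 6 months after, it is 6/12 = 0.50.

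**The case against.** The strongest reply is that the planned paired t test already answers the service question. It keeps patients with no change and tests the mean change, which is total use divided by n. The rate ratio gains at most 2 points over it in the table above. This stands: the criticism applies to the Wilcoxon branch. That the counts will go there is a likely inference from the rule, not something the protocol states.

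Second, dropping unchanged patients sounds worse than it is. Most of those dropped at low rates have no events in either window, and they add nothing to the point estimate of a before-after rate ratio either. This also stands. The loss lies mainly in replacing event numbers with ranks.

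Third, a reader might infer that neither planned test could cope with windows of different length. The document does not support that: both tests can be applied to per-patient rates. The analysis section also uses equal windows, and the missing-data section excludes patients with missing data, so observed time matters little there. It becomes important only for partial follow-up that is kept, or if the longer pre-clinic windows given elsewhere are used on raw counts.

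Finally, this is a single-arm quality-improvement evaluation whose size is set by clinic uptake, and the protocol also promises means or medians with 95% CIs. That lowers the stakes but does not make the statement correct. Nor can an unseen analysis plan excuse it as an omission, because this document itself fixes the variable type and the test.

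**Conclusion.** The statement that all listed outcomes are continuous is wrong for emergency-care use, and the test choice built on it is poorly matched to the question about health service use. This is a defect of estimand and efficiency, not of error control.

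Its size depends on where a benefit falls. With a uniform effect it costs almost nothing. With a fall confined to the top 10% of users, Wilcoxon loses about 17 percentage points of power against a rate ratio at mean 1 (69 − 52) and 19 at mean 2 (93 − 74), but only about 3 at mean 0.25. These figures rest on assumed gamma-Poisson counts with shape 0.7, n=500 and two-sided 0.05, because the protocol gives no event rates.

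A reader might go further and conclude that the planned analysis is invalid, or that it would generally miss or reverse a fall in total use. The document does not support this. The paired t branch remains available and targets the mean. The example in which the ranks lean the wrong way requires more patients to rise than to fall, a pattern the protocol gives no reason to expect.

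**What to change.** Remove emergency-care outcomes from the statement about continuous measures and from the paired t or Wilcoxon rule. Analyse them as paired event counts with a Poisson or negative binomial model, with patient-level robust standard errors or random effects. Report the after-to-before rate ratio with its 95% CI and the mean events per patient-year in each period. The questionnaire scores can keep their present tests.

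Include log observed time as an offset, so that partial follow-up and any unequal windows are handled as rates. Reconcile the windows in Aims and Objectives, in Patient Assessments and in the analysis section, so that one comparison is named for these outcomes. The same model can carry the calendar terms for the seasonal adjustment promised in the aims, which the analysis section does not take up.

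The cost is a few lines of analysis wording and standard software, with no new data. The Results section says analysis is already under way, so the count analysis should be dated and labelled as a change from plan, with the originally planned test reported beside it.
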